# Study Design

ASSET will be conducted as:

- **Three separate randomised controlled trials** in Auckland, Counties Manukau and Canterbury (there will be no control group in Tairawhiti)
- Within each of the active intervention arms, including Tairawhiti, there will be an **action research process to optimise the telecare system intervention.**
- Within each control arm there will be a **process of mapping real usual care.**

Each region will stand alone as a discrete trial though with some shared outcomes. Standard criteria and measures will apply across all trials.

The telecare equipment will be available to all four health services for 12 months, with equipment loaned to any one patient for up to three months.

Participants will be assessed at baseline with follow up at three (immediately post intervention) and six months (three months post intervention).

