# Baseline and repeated assessments

All study participants, in intervention and control groups, will have the same data collected relating to quality of life and resource use at baseline, 3 months and 6 months.

Those in the intervention arm will be asked additional questions relating to the technology, at 3 months and 6 months.

For baseline data collection see **Appendix 1**.

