# Randomisation and study group assignment

Immediately after baseline data collection, participants in Auckland and Counties Manukau will be randomised to intervention or control arms. The researcher will phone an Interactive Voice Response (IVR) system via an 0800 number, provide basic patient identification data and be assigned a study group for that patient.**

*Eligible  consent  baseline data collection  individual randomly assigned to intervention or control*

In Christchurch, a pre-assigned cluster randomisation will assign participating general practice surgeries – and the patients attending them – to intervention or control arms of the study.

*Eligible  consent  baseline data collection  cluster randomised to intervention or control, based on randomly assigned group of patient’s general practice*

In Tairawhiti, patients will not be assigned to separate groups.

*Eligible  consent  baseline data collection  followed in telecare programme*

Note: initially we intended to randomise with stratification by age / gender / distance from hospital / ethnicity. We have decided against this as i) we are collecting pilot data and will find if we obtain an adequate stratification by including all who are eligible and consent ii) there are technical and efficiency reasons not to stratify. From this pilot data we will be better informed as to whether stratification will be necessary in a follow up trial.

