**Sample size**

Each region will be a stand-alone and discrete trial though with some shared outcomes. Standard criteria and measures will apply across all trials. A sample size of 120 within Auckland, Counties Manukau and Canterbury will provide a power of 90% with alpha = 0.05 to detect a 10 point increase in SF36. Similarly, the literature (Bourbeau) suggests we need 86 patients in each study arm to have 90% power (alpha 0.05) to detect a mean change of 4 (the minimum important difference) on the St George Respiratory Questionnaire. Detecting some other outcomes will require more patients.

See separate document, “ASSET planning and power calculations” for details of data underlying power calculations.

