# Analysis

Primary quantitative analysis will be by Intention to Treat (i.e. as planned) and modified Intention to Treat (i.e. as delivered). Exploratory analysis will assess the influence and associations of explanatory and potentially confounding variables. The findings will help determine whether randomization for subsequent trials needs to be simple or stratified.

Subgroup analysis will be employed, where possible with the number of patients in each group, to detect clinically important differences between subgroups that may be defined by age, gender, ethnicity, rural-urban dwelling and severity of initial health assessments.

There will be no imputation of missing data. All analyses will be conducted in Stata. Continuous variables will be analysed using mixed effects models that included site as a fixed effect, patient as a random effect and adjusted for age and gender. The main outcome for the psychometric scales will be assessed from the interaction between intervention group and time. Negative binomial regressions will be used to model count data including numbers of hospital attendance, length of stay and costs in analyses were adjusted for patient age, gender, ethnicity, and site as a factor variable. Exposure, for hospital use, will be measured by days alive and not in hospital. Exposure, for total days in hospital, will be measured by days alive. Results will be considered statistically significant when p ≤ 0.05.

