# Appendix 2. Outcome measures

|  | Primary quantitative |  |
| --- | --- | --- |
| 1 | Number of hospital admissions in 1 year | DHB database |
|  | Number ED attendances | DHB database |
| 2 | Number of bed days in 1 year | DHB database |
| 3 | Deaths | DHB database |

|  | Secondary quantitative |  |
| --- | --- | --- |
| 4 | Change in hospital admissions from previous year | DHB database |

|  | Qualitative & descriptive |  |
| --- | --- | --- |
| 5 | Social problems identified and addressed | See interview schedules |
|  | Organisational processes | See interview schedules |
| 13 | Patient experiences | SF36, disease specific scales, interviews |
| 14 | Whanau / carers experiences | Interviews |
| 15 | Staff (include safety concerns) | Interviews, action research process and observations |

|  | Quality of Care |  |
| --- | --- | --- |
| 7 | Fidelity of care to intended model | Action research, interviews with staff |
| 8 | Measures of integration | Interviews with staff and researchers |
|  | Disease specific measures | To be advised by disease experts researchers |

|  | Costs, Resources |  |
| --- | --- | --- |
| 9 | Standard cost per admission | DHB accounting |
| 10 | Standard cost per bed day | DHB accounting, Patient Cost System |
| 11 | FTE staff on project | DHB management, log by researchers & staff |
| 12 | Additional costs - transport | Staff log |
| 16 | Staff Interventions | Staff diary |
|  | Costs of usual care | Log by staff |
|  | number of people / agencies visiting house | Researcher, patient interviews |
|  | Number of GP visits | Researcher, patients interviews |

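### Taking the psychometric effect from the group-by-time interaction, with no baseline adjustment, is unbiased but less precise than a baseline-adjusted estimate from the same data

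*Protocol*

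**What the plan says.** The Analysis section fits continuous outcomes with "mixed effects models that included site as a fixed effect, patient as a random effect and adjusted for age and gender". It then names the quantity of interest: "The main outcome for the psychometric scales will be assessed from the interaction between intervention group and time".

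Under Study Design: "Participants will be assessed at baseline with follow up at three (immediately post intervention) and six months (three months post intervention". Under Baseline and repeated assessments, all participants in both arms "will have the same data collected relating to quality of life and resource use at baseline, 3 months and 6 months". Under Randomisation: "Immediately after baseline data collection, participants in Auckland and Counties Manukau will be randomised to intervention or control arms". Canterbury differs: general practices are allocated in advance, and a patient takes the arm of their practice.

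For counts, the Analysis section uses negative binomial models adjusted for age, gender, ethnicity and site. Appendix 2 (item 4) lists a secondary outcome, "Change in hospital admissions from previous year", taken from the DHB database. The previous-year figure is not listed as a covariate.

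The Sample size section says that 120 per region "will provide a power of 90% with alpha = 0.05 to detect a 10 point increase in SF36". It gives neither an SD nor a baseline-to-follow-up correlation and refers to a separate planning document.

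**The concern.** An interaction with time expresses a treatment effect only if baseline is one of the response times. If only 3 and 6 months were responses, it would measure how the effect changes between those two visits. So the stated method implies that baseline sits on the response side. With no common baseline mean stated and no baseline covariate listed, the interaction at a given visit is the difference between arms in change from baseline.

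In Auckland and Counties Manukau, baseline is collected before individual randomisation, so the expected baseline means are equal by design. A free group difference at baseline ignores that and pays for it in variance. The count models leave a similar gain unused: previous-year admissions are to be retrieved but serve only to form a change outcome.

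Precision is at stake. Each region is a stand-alone trial of modest size, and the results are meant to inform effect sizes for later trials.

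**Working it through.** **Inputs.** From the protocol: 120 per region (60 per arm at the 1:1 allocation in Appendix 8), 90% power, alpha 0.05, 10 SF-36 points; and for the St George questionnaire, "we need 86 patients in each study arm to have 90% power (alpha 0.05) to detect a mean change of 4" points. Assumed: two-sided alpha, normal approximation, rho from 0.3 to 0.9, equal variance at each visit, complete data, visit as a category, individual randomisation.

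**The plan's own figure.** With no SD stated, 120 cannot be reproduced, only back-solved:

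SD = 10 × √(60/2) / (1.960 + 1.282) = 54.77 / 3.242 ≈ 16.9

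The same step for the St George figure gives 4 × √(86/2) / 3.242 ≈ 8.09.

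**Variances**, in units of 2σ²/n with n per arm:

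- interaction with a free baseline difference (difference in change): 2(1 − rho)
- baseline-adjusted: 1 − rho²
- ratio adjusted/interaction: (1 − rho²) / [2(1 − rho)] = (1 + rho)/2

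Generalised least squares with a patient random intercept and visits at 0, 3 and 6 months confirms this. The 3-month interaction has variance 1.40, 1.00 and 0.60 at rho 0.3, 0.5 and 0.7. With a common baseline mean, the same data give 0.91, 0.75 and 0.51, which equal 1 − rho².

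**Size at 60 per arm**, 10 points, SD 16.9 taken as cross-sectional. Each pair is interaction / adjusted:

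| rho | Variance ratio | Excess SE | SE (points) | Power | n per arm for 90% |
|---|---|---|---|---|---|
| 0.3 | 0.65 | 24% | 3.65 / 2.94 | 78% / 92.5% | 84 / 55 |
| 0.5 | 0.75 | 15% | 3.09 / 2.67 | 90% / 96% | 60 / 45 |
| 0.7 | 0.85 | 8% | 2.39 / 2.20 | 98.7% / 99.5% | 37 / 31 |
| 0.9 | 0.95 | 3% | 1.38 / 1.35 | 100% / 100% (rounded) | 12 / 12 |

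Example at rho 0.3: interaction SE = 16.9 × √(1.40 × 2/60) = 3.65; adjusted SE = 16.9 × √(0.91 × 2/60) = 2.94.

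Below rho 0.5, 2(1 − rho) exceeds 1, so the interaction is less precise even than comparing follow-up scores with no use of baseline.

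**If the implied SD is an SD of change.** The interaction then has 90% power at the stated n whatever rho is, and the ratio (1 + rho)/2 still applies. For the St George figure, 86 per arm would become 65 at rho 0.5 (86 × 0.75 = 64.5) or 74 at rho 0.7 (86 × 0.85 = 73.1).

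**The case against.** The strongest reply is that a group-by-time interaction is a standard, valid analysis, that ASSET is described as a pilot not powered for most outcomes, and that parameterisation is normally left to an analysis plan. A model with equal baseline means is also read from group-by-visit terms, so the sentence does not exclude it.

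Much of this stands. The free baseline difference is the ordinary reading, not an explicit statement, and the gain is small when rho is high. But the protocol names both the quantity and the adjustment variables. That is a stated choice, not an omission, and a better use of data already collected is available.

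Four stronger readings are tempting, and the documents do not support them.

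- *The estimate is biased, because change scores over-correct through regression to the mean.* That describes what happens given a chance imbalance. Over randomisation the interaction is unbiased.
- *Baseline means can be set equal in all three trials.* In Canterbury, practices are allocated before patients are recruited, and the researcher reads the arm from the practice. Recruitment could differ between arms, so equality is not secure. If sites are pooled, the constraint would carry that weakness into the pooled estimate.
- *The interaction pulls power down to about 82%, against 92% adjusted.* Those figures (rho 0.5, t-test, SD 16.76) apply an SD back-solved from 60 per arm to the 48 per arm in Appendix 8. At 60 per arm and rho 0.5, the interaction has the intended 90%. The fall to 82% comes from the smaller number, which is a separate matter.
- *Every count model can take its previous-year value at no cost.* Appendix 2 lists a previous-year figure for hospital admissions only, not for ED attendances or bed days.

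**Conclusion.** The point holds as a loss of precision, not as a validity error. The planned interaction has a standard error about 24%, 15%, 8% and 3% larger than needed at rho 0.3, 0.5, 0.7 and 0.9. The benefit of adjusting is therefore material at low to moderate correlation and slight at high correlation.

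The ratio rests on complete data, visit as a category and individual randomisation. Dropout or linear time makes it approximate, in the same direction. It does not carry over exactly to Canterbury. The power figures rest further on the back-solved SD being cross-sectional. No size can be given for the admissions model, because the documents give no correlation between previous-year and study-year admissions.

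**What to change.** In the Analysis section, replace the interaction sentence with wording to this effect: for each psychometric scale, the treatment effect is the between-arm difference at 3 months, and separately at 6 months, estimated from the mixed model with visit as a category and the baseline score as a covariate.

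A model with baseline as a response and equal baseline means across arms may be used instead in Auckland and Counties Manukau only, not in Canterbury and not in any model that pools Canterbury with them. The baseline covariate does not impose equal means, though it would not by itself remove a recruitment difference between practices.

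In the negative binomial model for hospital admissions, add the previous-year admission count as a covariate. Extend this to ED attendances or bed days only if their previous-year values are also retrieved.

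The cost is a wording change. No patients, visits or questionnaires are added, and for admissions the previous-year figure is already to be retrieved. Extending it to other counts would need an extra database extract.

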**Qualitative analysis**

Qualitative analysis will be principally use thematic analysis, where the themes are derived from the purposes of the project; themes are implied in most of the questions in the qualitative interview schedules, as the questions themselves are mostly the results of others’ qualitative analyses.

**Cost-effectiveness telecare and usual care**

Analyses will be performed to ascertain the robustness of any cost-utility differences found between the programmes based on this costing procedure. This will include the following tests:

1. Varying the projected technology costs to determine sensitivity to return on investment
2. Varying the percentage of costs assumed for staff costs and related overheads
3. Total versus marginal costs for the different programmes
4. Varying the costs attributed to informal care

**Cost utility analysis**

Model of how much time looking after telecare pt should take v how long it took to actually do and resources involved? What was taking us 3 hours now takes us 2. Ie modelling after learning has taken place and reached a ‘steady state’.

# Summary of data collection at each time point

|  | **At beginning of each patient telemonitoring** | **At end of each patient telemonitoring** | **At end of project** |
| --- | --- | --- | --- |
| **patients** | **Baseline data collection**  **SF36**  **Stanford self-efficacy scale**  **Semistructured interview based on PIH**  **Disease specific questionnaire**  **1. St George Respiratory Questionnaire**  **2. COPD Helplessness Index**  **3. Minnesota Heart Failure questionnaire (?)** | **SF36**  **Stanford self-efficacy scale**  **Semistructured interview based on PIH**  **Disease specific questionnaire**  **1. St George Respiratory Questionnaire**  **2. COPD Helplessness Index**  **3. Minnesota Heart Failure questionnaire (?)** |  |
| **Patient whanau / support people** | **Semistructured interview based on PIH** | **Semistructured interview based on PIH** |  |
| **clinicians** |  |  |  |
| **Clinicians, administrators** |  |  |  |
| **Research team** |  |  | **Interview using REFLECT model** |

# Timeline

| ID | Name | Start | Finish |
| --- | --- | --- | --- |
| 1 | Planning and ethics |  |  |
|  | Detailed protocol | Nov 09 |  |
| 4 | Development of interviews and questionnaires | Dec 09 |  |
|  | Maori consultation | Jan 10 |  |
| 2 | Ethics application | Jan 10 |  |
|  | Vendor contracts signed | Feb 10 |  |
|  | Delivery of first equipment | Mar 10 |  |
| 3 | Recruitment of staff | Feb 10 |  |
|  | Testing of equipment | Mar 10 |  |
|  | Training for equipment | Mar 10 |  |
|  | Training for research protocol, interviewing, questionnaire admin | Mar 10 |  |
| 5 | Data collection |  |  |
|  | First rollout | May 10 |  |
|  | Second rollout | Jun 10 |  |
|  | Third rollout | Jul 10 |  |
| 17 | Analysis and reports |  |  |
| 18 | Data analysis |  |  |
| 20 | Draft report |  |  |
| 21 | Final report |  |  |

# References

# Appendix 1. Baseline data collection

**Patients and family / whanau**

Date of birth, age, Gender

Ethnicity – self-assigned using standard census question

Address, Contact details

Marital status, Household members

Household member / Caregiver details, contacts details

Highest education

Employment status, current and past main employment

Income or benefit status

Social support (eg home help)

Health care support (including GP)

Index condition

Other morbidities

Random assignment group

# Appendix 2. Outcome measures

|  | Primary quantitative |  |
| --- | --- | --- |
| 1 | Number of hospital admissions in 1 year | DHB database |
|  | Number ED attendances | DHB database |
| 2 | Number of bed days in 1 year | DHB database |
| 3 | Deaths | DHB database |

|  | Secondary quantitative |  |
| --- | --- | --- |
| 4 | Change in hospital admissions from previous year | DHB database |

|  | Qualitative & descriptive |  |
| --- | --- | --- |
| 5 | Social problems identified and addressed | See interview schedules |
|  | Organisational processes | See interview schedules |
| 13 | Patient experiences | SF36, disease specific scales, interviews |
| 14 | Whanau / carers experiences | Interviews |
| 15 | Staff (include safety concerns) | Interviews, action research process and observations |

|  | Quality of Care |  |
| --- | --- | --- |
| 7 | Fidelity of care to intended model | Action research, interviews with staff |
| 8 | Measures of integration | Interviews with staff and researchers |
|  | Disease specific measures | To be advised by disease experts researchers |

|  | Costs, Resources |  |
| --- | --- | --- |
| 9 | Standard cost per admission | DHB accounting |
| 10 | Standard cost per bed day | DHB accounting, Patient Cost System |
| 11 | FTE staff on project | DHB management, log by researchers & staff |
| 12 | Additional costs - transport | Staff log |
| 16 | Staff Interventions | Staff diary |
|  | Costs of usual care | Log by staff |
|  | number of people / agencies visiting house | Researcher, patient interviews |
|  | Number of GP visits | Researcher, patients interviews |

# Appendix 3. Interview schedules

**Interviews with patients, about self-care, at the beginning and end of their telemonitoring**

Semi-structured interviews with patients, based on 12 areas of the Flinders Partners in Health Scale.6

1. Knowledge of condition
2. Knowledge of treatment
3. Ability to take medication
4. Ability to share in decisions
5. Ability to arrange and attend appointments
6. Understanding of monitoring and recording
7. Ability to monitor and record
8. Understanding of symptom management
9. Ability to manage symptoms
10. Ability to manage the physical impact
11. Ability to manage the social and emotional impact
12. Progress towards a healthy lifestyle.

**Interviews with patients, about their perceptions of the technology, at the end of their telemonitoring**

Semi-structured interview to establish perceptions about usefulness of the technology (based on protocol by Rahimapour et al 7, and added to by considerations suggested by Kaplan & Shaw 5 and van der Loo et al 4).

Participants will be asked about

- Their overall attitude toward the telemonitoring technology – do they like it and what do they like?
- Perceptions about how easy/difficult it is to use the technology, and what they feel are advantages/disadvantages to using it. What their preferences are regarding using the technology.
- Their confidence in using the technology and any possible barriers to building confidence. Any abilities they consider essential for using the technology? What would make them not be able to use the technology?
- How they perceive the technology could help them manage their health.
- How they feel the technology would help them gain more knowledge about their health/chronic condition.
- Perceptions about their clinicians’ use of the technology and the resulting information about them.
- Sense of distance of clinicians now that they are not cared for in hospital. How do they feel about the reduction in face-to-face communication with their clinicians?
- Concerns about privacy and/or confidentiality.
- Their training experience and how they felt it could be improved.
- Their perception on how this technology may changedor has changed their hospitalisations and/or use of emergency care centre.
- Sense of impact on costs to themselves and/or the healthcare services they use.
- Perception of impact of the technology on their time – how does the technology change the way they use their time for self care and/or care delivered by others to them?
- Sense of how the technology impacts on their family, Whanau, friendships and work relationships (for those who are employed).
- Unintended consequences, unexpected experiences, e.g. performance of the technology.
- Perception of satisfaction with the technology and associated care processes.
- Knowing what they know now, why would they use telemonitoring again if they got an opportunity?

**Interviews with health care providers, perceptions of the projected, after one year.**

Semi-structured interview schedule for clinicians, managers and administrators associated with the telemonitoring project, and will cover the changes, assumptions, expectations, outcomes and unintended consequences of the project. Questions based on findings of Kaplan & Shaw 5, Ammenwerth et al 3, van der Loo et al 4 and Callen & Westbrook 16.

- Reflect on and document their understanding of the implications of the consequences of telemonitoring on ‘usual care’ processes
- Create guidelines for inclusion of patients in telemonitoring and exit criteria for terminating telemonitoring
- Reflect on the project management implications, requirements and critical success factors for implementing telemonitoring, and identifying the requirements for upscaling telemonitoring as a national initiative.
- Indicate if their sense of job satisfaction has been influenced by the use of telemonitoring
- Reflect on perceptions of usefulness of the technology and resulting information flows, and whether the technology delivered what was expected.
- Consider if/how the use of the technology changed/improved the quality of care for their patients
- The role of policy and culture on the intention to use telemonitoring as a chronic condition management intervention, and how these need to change to ensure further adoption
- What problem areas are there regarding daily use of the technology? Any pitfalls, and solutions?
- Is the technology usable in the intended environment and is it used as intended?
- Why did the outcomes (clinical, process, organisational, protocols) happen the way they did?
- Unintended consequences, unexpected experiences, e.g. performance of the technology.
- Knowing what you know now (after a year), why would you continue to use telemonitoring? What would they improve/change?

